## Abstract

**Background:**

Evidence for early intensive behavioural interventions (EIBI) by therapists as an effective treatment for children with an Autism Spectrum Disorder (ASD) is growing. High-intensity and sustained delivery of quality EIBI is expensive. The TOBY (Therapy Outcomes by You) Playpad is an App-based platform delivering EIBI to facilitate learning for young children with ASD, while enabling parents to become co-therapists. Intervention targets include increasing joint attention, imitation and communication of children with ASD. The primary aim of the study presented in this protocol is to determine the effectiveness of the TOBY App in reducing ASD symptoms when used as a complement to conventional EIBI. The secondary aim is to examine parental attributes as a result of TOBY App use.

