**Discussion:**

This trial will determine the effectiveness of the TOBY App as a therapeutic complement to other early interventions children with ASD receive. The trial will also determine the feasibility of a parent delivered early intervention using the iPad as an educational platform, and assess the impact of the TOBY App on parents’ self-efficacy and empowerment in an effort to reduce children’s ASD symptoms. The outcomes of this trial may have EIBI services implications for newly diagnosed children with ASD and parents.

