
The objectives of this study are:To determine the effectiveness of the TOBY Playpad App as a complement to early behavioural intervention as measured by a range of psychometric assessments which will assess core symptomology of ASD across time (baseline (Time 0), 3 months follow-up (Time 1) and 6 months follow-up (Time 2) through in-App data and parent reports.To determine whether the response to TOBY varies with variation of treatment intensity across both, TOBY + ‘therapy as usual’, and across different TOBY learning environments and syllabus.To measure the uptake of the TOBY intervention as recorded by the App and assessed by parents throughout the trial period using parent therapy diaries.To examine attitudes, perceptions and beliefs of parents towards TOBY as an intervention method as assessed by specific TOBY, family and parenting questionnaires over 6 months.To determine if TOBY intervention impacts on parental empowerment and stress levels.

We hypothesize that the TOBY App will improve children’s adaptive behaviours (language; social communication; restricted and repetitive behaviours) over time as assessed by a variety of measures at the final follow-up (6 months after starting the TOBY intervention). We also predict that parental empowerment in relation to the delivery of TOBY therapy will be enhanced at 6 months post randomisation. In addition, parental stress levels will be reduced as a result of the uptake of the TOBY intervention.

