### Inclusion criteria

*Children aged less than 4;3 months (51 months)*: At the time of screening for eligibility, potential participants’ age would be less than 4 years and 3 months. In Australia, the average age of a child with ASD at the time of formal diagnosis is 49 months [13]. The early key developmental areas that are primarily targeted by the TOBY intervention used in this trial calls for the inclusion of young children and their primary caregivers as necessary participants for this study.
*Diagnosis of autism spectrum disorder:* Participants will be children who receive a clinical diagnosis of ASD according to DSM-IV-TR or DSM-V guidelines [56, 57] within the 12 months prior to the time of screening for eligibility. This post diagnostic time is a critical period for families affected by ASD where acceptance and management of the new developmental diagnosis is coupled with many decision making processes including which of a variety of disability agencies to access in a bid to seek funding, support and gauge treatment options. Families are typically wait listed for early intervention therapies that are supported by state jurisdictions, the Commonwealth of Australia or private therapy providers. The wait list period for ASD specific treatment services can vary greatly between states and regions for both, state or privately funded operators. For this trial, participants’ clinical diagnosis of ASD will be validated as part of baseline battery of assessments and will include children who also meet the diagnostic criteria for autism or autism spectrum on the Autism Diagnostic Observation Schedule – Generic (ADOS-G) [58] or the ADOS-2 algorithm [59] for DSM-IV/ICD-10 or DSM-V/ICD-11 [56, 57].

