## Intervention

### Treatment group: TOBY therapy + therapy as usual group

This group of participants will receive treatment in the form of the TOBY Playpad intervention over 24 weeks, in addition to any other type of early intervention that the family and child are accessing upon entry to the trial. The TOBY Playpad intervention will be used solely or as a complement to ‘therapy as usual’. The TOBY Playpad (http://tobyplaypad.com/about/) is a unique early intervention program for children with ASD and other neurodevelopmental disorders. Currently, the TOBY Playpad is only accessible through an iOS-based device such as an iPod/iPad® App. The software, user interface, and theoretical underpinning of the TOBY syllabus including experimental evaluation of this assistive technology are described elsewhere [52, 53]. The TOBY (referred to from here) delivers a curriculum based on the principles of EIBI and evidence-based learning strategies. The TOBY curriculum contains a variety of user-generated and automated on-and off-iPad lessons. The TOBY is designed as an educational early intervention program for parents of newly diagnosed children with ASD and an automated (machine based) therapist for the child. The TOBY intervention is delivered in the following ways, through the availability of 30 on-iPad/on-screen and 300 off-iPad tasks. This can occur across three learning environments; 1) child only (solo), 2) parent and child (partner) or, 3) the Natural Environment Tasks (NET). The TOBY syllabus is designed to teach 52 foundation skills across four main learning areas (Sensory; Imitation; Language and Social) which are required for optimal language, communication, play and cognitive early childhood development. All TOBY lessons and tasks are developmentally sequenced to accelerate early learning and monitored by the App [52].

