### Control group: therapy as usual

This group of children and parents will not receive the TOBY intervention. They will continue to receive their regular early intervention or may commence other type of early intervention therapy of their choice during the trial period. This group of participants will undergo the same number and order of direct assessments as the treatment group. They will also complete the same questionnaires and assessments as the TOBY therapy group at three and six months. The study coordinator will remind parents to record all early intervention therapies (‘therapy as usual’) that their child is receiving in the provided diaries.

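### The primary aim is worded as TOBY on top of conventional EIBI, but the randomised comparison is TOBY added to any community therapy, possibly none, so it cannot support an EIBI-specific conclusion

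*Protocol article*

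**What the plan says.** The Abstract (Background) states the primary aim: "to determine the effectiveness of the TOBY App in reducing ASD symptoms when used as a complement to conventional EIBI". The first objective, at the end of the main Background section, is close to it: "To determine the effectiveness of the TOBY Playpad App as a complement to early behavioural intervention".

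The sections that define the trial are broader:

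- **Inclusion and Exclusion criteria** cover age, recent diagnosis, previous TOBY use and medical conditions. None concerns current therapy. Of the period after diagnosis, the Inclusion criteria say: "Families are typically wait listed for early intervention therapies".
- **Study design** defines the control condition as early intervention of any kind obtained from local providers.
- **Treatment group** says: "The TOBY Playpad intervention will be used solely or as a complement to" therapy as usual.
- **Control group** says that families continue their regular intervention or "may commence other type of early intervention therapy of their choice during the trial period".
- **Randomisation and blinding** stratifies by site, socio-economic status and developmental quotient, not by therapy status.

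The Abstract (Discussion) words the expected conclusion more widely than the aim: "the effectiveness of the TOBY App as a therapeutic complement to other early interventions children with ASD receive".

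**The concern.** An aim that names a background therapy commits the report to a claim about children receiving that therapy. Here the enrolled population is not defined by it. The main Background section says that services in many developed countries, Australia included, cannot offer intensive EIBI to newly diagnosed children, and that many families are constrained in getting it. Newly diagnosed children are the ones the trial recruits.

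If the aim stands as written, a positive result would naturally be reported as benefit on top of conventional EIBI, although it might come largely from children receiving other therapy or none. A null result would likewise be read as no added value over EIBI, although few children may have been receiving it. The Abstract (Discussion) expects implications for EIBI services, so the difference affects how the result would be used.

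**Working it through.** **1. Aim and design side by side**

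| Element | Background therapy named or required |
|---|---|
| Primary aim (Abstract, Background) | Conventional EIBI |
| Objective 1 (Background) | Early behavioural intervention |
| Eligibility | None required |
| Control arm (Study design) | Any early intervention |
| Treatment arm (Treatment group) | Any, or TOBY alone |
| Expected conclusion (Abstract, Discussion) | Other early interventions that the children receive |

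The first two rows are narrower than the three design rows below them. The last row is close to the design, apart from children who receive no other therapy.

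**2. The plan's own figure**

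Sample size and analyses gives about 64 per group for an effect of 0.2 to 0.5 with 80% power and two-sided alpha 0.05. A two-sample t-test at 0.5 SD needs 63.8, so 64; at 0.2 SD it needs 394. The stated figure reproduces at the upper end of the range. This does not decide the present point, but it gives the number of children used below.

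**3. What the overall effect says about EIBI recipients**

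Let f be the share of children on EIBI, the same in both arms. The documents do not give f, so the values here are assumptions. Then

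overall effect = f × (effect with EIBI) + (1 − f) × (effect without EIBI).

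At f = 0.5:

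- effects 0.5 and 0: 0.5 × 0.5 + 0.5 × 0 = 0.25 SD
- effects 0.25 and 0.25: 0.5 × 0.25 + 0.5 × 0.25 = 0.25 SD
- effects 0 and 0.5: 0.5 × 0 + 0.5 × 0.5 = 0.25 SD

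Three different answers to the stated aim give the same trial result. Over a range of f:

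| f | Overall effect if benefit (0.5 SD) only with EIBI: 0.5 × f | Overall effect if benefit (0.5 SD) only without EIBI: 0.5 × (1 − f) |
|---|---|---|
| 0.25 | 0.125 | 0.375 |
| 0.50 | 0.25 | 0.25 |
| 0.75 | 0.375 | 0.125 |

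Neither pattern is more plausible than the other on the documents. The table shows only that the overall contrast does not identify the EIBI-specific effect.

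**4. Could a subgroup answer it?**

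With 64 per arm analysed, a true effect of 0.5 SD and an analysis restricted to children on EIBI (64 × f per arm):

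| f | n per arm | Power |
|---|---|---|
| 0.75 | 48 | 68% |
| 0.50 | 32 | 50% |
| 0.25 | 16 | 28% |

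Such an analysis is exploratory at best.

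**5. What could define the subgroup?**

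In Table 1 the only measure described as recording therapy received is the daily diary, listed at T1 and T2. It is post-randomisation, and using TOBY may displace or prompt other therapy. The first diary week is no better. Under Parent training, treatment families receive the diary at a workshop held after randomisation and may then use the App in a test mode for up to 14 days. Controls have no TOBY start date to match. Objective 2 ("To determine whether the response to TOBY varies with variation of treatment intensity across both" TOBY and therapy as usual) does not help if it relies on the same diary hours.

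**The case against.** The strongest defence is that this is a declared pragmatic trial whose comparator is stated openly in several sections. Accepting any background therapy is a legitimate choice, and randomisation validly estimates the effect of adding TOBY to usual care. The main Discussion restates the primary aim without an EIBI background; there, EIBI describes TOBY itself. The Abstract's expected conclusion is also broad. On this view only two phrases are too narrow.

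Most of that stands, and it limits the point to the aim, the first objective and any conclusion drawn in their terms. Those phrases still matter, because one of them is the stated primary aim.

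Three stronger readings are tempting and are not supported:

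- **That the trial cannot support its intended conclusion.** It can support a conclusion about TOBY added to therapy as usual, which is close to the Abstract's Discussion. What it cannot support is the EIBI-specific version.
- **That nothing about therapy is recorded before randomisation.** The section on baseline assessments mentions questionnaires on support from services, an ambiguous phrase. Table 1 only summarises the intake and case-history forms. A record may exist.
- **That most enrolled children are untreated.** Being typically wait-listed is not the same as receiving nothing. The Inclusion criteria say that waits vary greatly, and the Treatment group section refers to therapy being accessed at entry. No proportion is given.

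**Conclusion.** The point holds as a mismatch between the stated aim and the population and comparator. The design answers whether adding TOBY to whatever community therapy a child receives, possibly none, changes outcome. It does not answer whether TOBY helps on top of conventional EIBI.

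The validity of the randomised comparison is not in question. The size of any misattribution cannot be derived from the documents, because the share on EIBI and any difference in effect by background therapy are unknown; the figures above are illustrations under assumed shares. The mismatch itself rests on the text alone.

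It is worth correcting before results are reported. Trial status says that data collection is complete and the data are being prepared for analysis. Eligibility can no longer change, but the wording of the claim can.

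**What to change.** 1. Restate the primary aim in the Abstract and the first objective as the effect of TOBY plus therapy as usual, of any type including none, versus therapy as usual. Word the resulting conclusion the same way.
2. Describe the therapy mix (type, format and time) by arm from the diaries already collected, as description only.
3. Make no claim of benefit on top of EIBI unless it comes from an analysis labelled exploratory that uses therapy status recorded before randomisation. First check whether the baseline forms hold such a record. If they do not, make no such claim.
4. Do not define subgroups from diary data, including the first diary week.

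The cost is a change of wording and one descriptive table, with no new data collection. The downside is a narrower claim about EIBI. Even where a baseline record exists, the exploratory analysis would be late-added and have low power.

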**Methods and design:**

Children aged less than 4;3 years diagnosed with ASD and parents will be recruited into this single-blind, randomised controlled trial using a pragmatic approach. Eligible participants will be randomised to the treatment group ‘TOBY therapy + therapy as usual’ or, the control group ‘therapy as usual’ for six months. The treatment will be provided by the TOBY App and parent where a combination of learning environments such as on-iPad child only (solo), partner (with parent) and off-iPad – Natural Environment (with parent) Tasks will be implemented. Parents in the treatment group will participate in a TOBY training workshop. Treatment fidelity will be monitored via an App-based reporting system and parent diaries. The primary outcome measure is the Autism Treatment Evaluation Checklist. The secondary outcome measures involve diagnostics, functional and developmental assessments, including parent questionnaires at baseline (T0), three months (T1) and six months (T2).

**Discussion:**

This trial will determine the effectiveness of the TOBY App as a therapeutic complement to other early interventions children with ASD receive. The trial will also determine the feasibility of a parent delivered early intervention using the iPad as an educational platform, and assess the impact of the TOBY App on parents’ self-efficacy and empowerment in an effort to reduce children’s ASD symptoms. The outcomes of this trial may have EIBI services implications for newly diagnosed children with ASD and parents.

**Trial registration:**

ACTRN12614000738628 retrospectively registered on 1^st^ of July, 2014. UTN: U1111-1158-6423.

## Background

The diagnosis of Autism Spectrum Disorder (ASD) in children is increasing globally [1–3], currently affecting approximately 1 % of the population [4–6]. ASD is characterised by social communication deficits and repetitive and restricted behaviours which place considerable psychological and financial pressures on primary care givers [7–10]. Early identification followed by clinical diagnosis of ASD typically occurs between the ages of 3 and 4 [11–13]. It is recommended that therapeutic intervention should soon follow diagnosis as early treatment has the ability to positively impact on young children’s neuroplasticity and thereby favourably alter developmental trajectories as evidenced in reports on the effectiveness of early intervention [14–18].

Empirical evidence for early intense behavioural intervention (EIBI) is now well established with significant and enduring impacts on the developmental and behavioural outcomes of young children with ASD [19–23]. A benchmark of EIBI of between 20 and 40 h per week for at least 2 years, targeting a range of pre-requisite developmental, adaptive and behavioural skills to harness optimal learning are recommended for children with ASD [15, 17, 24–26]. Early intervention services across many developed countries including Australia are unable to offer such intensive services to newly diagnosed children with ASD [27–29] due to shortfalls in trained staff and high costs associated with intensive therapy over an extended or indefinite periods of time [10]. Therefore, many families of young children with ASD are significantly constrained in their capacity to access EIBI. Long wait lists for early therapy services coupled with high ‘out of pocket’ costs limit families’ capacity to start and continue with early intervention. Since parents or primary care givers usually spend the greatest amount of time interacting with their children, they are in the best position to intervene and capitalise on their children’s neuroplasticity. Educating parents to become therapists for their children with ASD is not a new concept [30–35] and this approach may have lasting effects on early intervention outcomes [36–39]. Coaching parents to effectively engage, scaffold, prompt and reinforce communication and language can provide them with powerful skill-set for supporting their young children’s development and learning. This has been shown in studies focused on parent training of children with ASD using the principles of psychosocial and behavioural approaches [40–42] to facilitate behaviour change [40, 41, 43, 44] and to shift developmental trajectories [21, 45]. Parental involvement in early therapy has also been shown to reduce parental stress, enhance parental satisfaction and increase their confidence to harness opportunities for daily incidental learning for their children [46, 47].

Alongside EIBI and parent training, the proliferation of technology into the field of ASD treatment is growing. The development of touch screen tablets such as the iPad® has reimagined the portability, accessibility, affordability and social acceptance of obtaining information and education via this platform. Technology-based interventions and knowledge about autism treatment has seen some success in increasing communication skills among children with ASD by a way of augmentative alternative communication (AAC) or, on-screen social information [48–50]. Most recent report suggests that there are approximately 150 Apps that qualify for educational interventions using touch screen tablets [51]. As the technology market share and consumer base increases, new Apps are being developed and tested continuously. A systematic review of 15 studies focused on App-based interventions with individuals with ASD showed that the majority of these Apps were aimed at teaching academic, communication, leisure, activity transitions and employment skills [48]. However, few of these intervention Apps are underpinned by theoretical foundations about childhood development or provide evidence-based education for parents and the child with ASD in a variety of learning environments beyond conventional screen-based learning. Even fewer of these existing App-based interventions systematically monitor the child’s learning or provide feedback and guidance on the skills that the child is learning, or what the child should learn next. But, an intervention App that is consistent with key features of a comprehensive, individualised and quality EIBI is called the TOBY (Therapy Outcomes by You) Playpad App [52–54]. The TOBY App can be used by children or parents at any time solely, or in conjunction with other early intervention programs. Therefore, there is a potential saving of time and costs of the TOBY App over traditional EIBI that is typically expensive and delivered by a trained therapist coupled with parent education. A pilot evaluation of the TOBY App involving 33 families of children (age ≤ 16) with ASD were asked to use the App for six weeks without further instructions. This study showed high uptake of the TOBY App by parents with a consistent pattern of use throughout the TOBY curriculum [55]. However, lack of independent pre-post measures of children’s ASD characteristics and functioning as well as control group limited this study’s ability to determine change and evaluate the impact of the App on children’s development. Therefore, a large pragmatic trial is required to determine if the TOBY Playpad App can reduce core and non-core symptoms of ASD in newly diagnosed children in the community.

The objectives of this study are:To determine the effectiveness of the TOBY Playpad App as a complement to early behavioural intervention as measured by a range of psychometric assessments which will assess core symptomology of ASD across time (baseline (Time 0), 3 months follow-up (Time 1) and 6 months follow-up (Time 2) through in-App data and parent reports.To determine whether the response to TOBY varies with variation of treatment intensity across both, TOBY + ‘therapy as usual’, and across different TOBY learning environments and syllabus.To measure the uptake of the TOBY intervention as recorded by the App and assessed by parents throughout the trial period using parent therapy diaries.To examine attitudes, perceptions and beliefs of parents towards TOBY as an intervention method as assessed by specific TOBY, family and parenting questionnaires over 6 months.To determine if TOBY intervention impacts on parental empowerment and stress levels.

We hypothesize that the TOBY App will improve children’s adaptive behaviours (language; social communication; restricted and repetitive behaviours) over time as assessed by a variety of measures at the final follow-up (6 months after starting the TOBY intervention). We also predict that parental empowerment in relation to the delivery of TOBY therapy will be enhanced at 6 months post randomisation. In addition, parental stress levels will be reduced as a result of the uptake of the TOBY intervention.

